# **8 Assessments, Materials and Methods**

All assessments will be performed in an outpatient setting.

## **8.1 Clinical Assessments**

### **8.1.1 Efficacy Assessments**

Clinical efficacy assessments will include:

- Audiometric evaluation
- Occurrence and severity of tinnitus
- Video- or electronystagmography or Frenzel goggles
- Patient assessment of change in hearing impairment

|                                |                             |                      |
|--------------------------------|-----------------------------|----------------------|
| Protocol Amendment 7.1         | Study no.: NM-V-101         | Page 43 of 85 |
| Date of Amendment: 15 Feb 2018 | EudraCT No.: 2012-000066-37 |                      |

- Physician assessment of change in hearing impairment

### **Audiometric evaluation**

Audiometric tests will include standard air and bone conduction PTA.

Speech intelligibility test: Specific national test per country to determine the dB value where 50 % of single words will be understood.

### **Tinnitus**

The occurrence and the degree of problems that tinnitus will be quantified using a numerical rating scale.

### **Vertigo**

For assessment of vertigo, oculomotor function will be evaluated using videonystagmography or electronystagmography over 30 seconds. Frencl's goggles for assessment of vertigo are possible as well.

### **Patient Assessment of Change**

At Visits 1, 5, 6, and 7 (Days 1, 8, 30, 90, or early withdrawal visit), the patient will assess his/her change in hearing ability using a numerical rating scale.

### **Physician Assessment of Change**

At Visits 1, 5, 6, and 7 (Days 1, 8, 30, 90, or early withdrawal visit), the physician will assess the patient's change in hearing ability using a numerical rating scale.

### **8.1.2 Safety Assessments**

Clinical safety assessments will include:

- AE reporting.
- Changes from screening (Day 1; Visit 1) to Day 8 in general physical and otolaryngological examination findings.
- Changes from screening (Day 1; Visit 1) to Day 8 in vital signs.

### **Adverse Event Reporting**

Incidences and types of AEs will be recorded in the CRF through Day 90 after initiation of study drug as described in Section 9.1.

|                                |                             |                      |
|--------------------------------|-----------------------------|----------------------|
| Protocol Amendment 7.1         | Study no.: NM-V-101         | Page 44 of 85 |
| Date of Amendment: 15 Feb 2018 | EudraCT No.: 2012-000066-37 |                      |

## **General Physical and Otolaryngological Examination**

The following assessments will be performed on Day 1 (Visit 1) and Day 8 (Visit 5):

### **Physical examination**

The examination should include at least the following:

- General appearance (including lymphatic nodes)
- HEENT (head, eyes, ears, nose and throat)
- Cardiovascular
- Respiratory
- Gastrointestinal/Abdomen
- Musculoskeletal
- Skin/Dermatological
- Neurologic
- Other examinations

The physical examination is appropriate to record typical and possible adverse events (e.g. dermatorrhagia, bronchoconstriction). The patient has to be informed, how to detect clinical signs of adverse events and to contact the investigator in case of upcoming events.

### **Otolaryngological examination**

- Otoacoustic emissions
- Tympanometry
- Stapedius reflex measurement
- Ear microscopy

### **Vital Signs**

- Blood pressure
- Pulse rate
- Body weight
- Height (only at screening)

|                                |                             |                      |
|--------------------------------|-----------------------------|----------------------|
| Protocol Amendment 7.1         | Study no.: NM-V-101         | Page 45 of 85 |
| Date of Amendment: 15 Feb 2018 | EudraCT No.: 2012-000066-37 |                      |

## **8.2 Laboratory Assessments**

### **8.2.1 Efficacy Assessments**

Inflammatory and cellular markers will be determined as efficacy laboratory assessments in a central laboratory. Blood samples for inflammatory and cellular markers will be drawn prior to study drug infusion (baseline value at screening) and 8 days (Visit 5) after initiation of study drug infusion.

The following parameters will be analysed as surrogate parameters for efficacy:

- Inflammatory markers: interleukin-6, TNF- $\alpha$
- Molecular markers of leucocyte activation: CD38+, CD40+ cells

Inflammatory and cellular markers will be correlated with clinical effects.

### **8.2.2 Safety Assessments**

Laboratory safety assessments will be performed on the changes in the following laboratory parameters.

#### **Coagulation**

Blood samples for coagulation (Fibrinogen according to Clauss, TT, PT and aPTT) will be drawn prior to study drug infusion (baseline value at screening), two days (Visit 2) and 8 days (Visit 5) after initiation of study drug. Coagulation parameters during screening are used for the determination of the duration of study drug infusion and will be assessed in the local laboratory. The following measurements will be performed in the selected laboratory (local or central) of the site.

#### **Hematology, Clinical Chemistry, Urinalysis, and Pregnancy Test**

Venous blood samples will be drawn for the assessment of safety laboratory parameters and biomarkers on Day 1 (Visit 1) and Day 8 (Visit 5). The individual parameters will be assessed in the responsible laboratory as follows:

##### **Hematology**

Venous blood samples will be drawn for the assessment of the following parameters on Day 1 (Visit 1) and Day 8 (Visit 5): erythrocytes, hematocrit, MCV, leucocytes, erythrocyte sedimentation rate, hemoglobin, thrombocytes.

|                                |                             |                      |
|--------------------------------|-----------------------------|----------------------|
| Protocol Amendment 7.1         | Study no.: NM-V-101         | Page 46 of 85 |
| Date of Amendment: 15 Feb 2018 | EudraCT No.: 2012-000066-37 |                      |

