Ancrod (international non-proprietary name, INN) is an enzyme isolated from the venom of the Malayan pit viper *Calloselasma rhodostoma*. It causes a dose-dependent long-lasting anticoagulant effect by decreasing the blood fibrinogen concentration. Therapeutically induced and controlled hypofibrinogenemia diminishes the plasma viscosity and tendency of erythrocytes to aggregate so far that the flow properties of the blood in the microcirculation are crucially improved (Ehrly, 1973). Ancrod had been approved and marketed for more than 15 years in Canada and Europe as treatment for peripheral vascular disease, deep vein thrombosis, central retinal vein thrombosis, and as prophylaxis in subjects at risk for thromboembolism. Due to commercial reasons the owners of the marketing allowance, Knoll/BASF Pharma AG, withdrew ancrod from the market in June 2000.

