#### **2.4.2 Potential Benefits**

The therapeutic value of the frequently used oral or intratympanal steroids for the treatment of sudden hearing loss remains unclear (Wei et al., 2006). Other presently used therapies have not been confirmed in state-of-the-art double-blind randomized clinical trials and did therefore not obtain regulatory approval. The existing treatment options for SSHL may thus be comparable to the placebo treatment arm in the planned clinical study.

In contrast, clinical data obtained from a study with batroxobin, a serine protease derived from another snake venom and with similar mode of action as ancrod revealed a good treatment effect in patients with moderate to severe hearing loss. The improvement was significantly better in patients on batroxobin than in patients receiving corticosteroid treatment.

Ancrod's therapeutic benefit lies in its fibrinogenolytic action which causes reduced plasma fibrinogen concentration, associated with a progressively reduced blood viscosity by 30-40% of the pretreatment levels (Ernst and Dormandy, 1981). The diminished viscosity leads to an

|                                |                             |                      |
|--------------------------------|-----------------------------|----------------------|
| Protocol Amendment 7.1         | Study no.: NM-V-101         | Page 24 of 85 |
| Date of Amendment: 15 Feb 2018 | EudraCT No.: 2012-000066-37 |                      |

improvement in microcirculation. These rheological changes are sustained and viscosity approaches pretreatment values approximately 10 days after termination of ancrod treatment.

The treatment of SSHL with ancrod represents a novel approach which is expected to exhibit:

- better efficacy than existing therapies
- favorable safety profile
- good patient compliance due to simple dosing regimen

Thus, for each subject, the possibility of a positive therapeutic effect and his or her contribution to the scientific understanding of the properties and actions of ancrod are the only benefits.

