On Day 8 (Visit 5) the treatment effect will be evaluated by means of audiometry and speech recognition, and the presence and intensity of tinnitus and vertigo will be determined. In addition, a blood sample will be taken for coagulation assays and biomarkers will be measured. The result of the coagulation assay may in principle not be communicated from the laboratory to the investigator or any other blinded study personnel. If, on Day 8 (Visit 5), no improvement of clinical signs and symptoms compared to the baseline value has been achieved, the patient will be allowed to switch to corticosteroid treatment, vasodilators, vitamin C, vitamin B12 or antihistamines if deemed necessary at the discretion of the investigator.

During the follow-up visits on Day 30 and Day 90 (Visits 6 and 7) the treatment effect will again be determined by audiometric evaluation and tinnitus intensity to monitor for signs of relapse in the affected ear. Comparison of this audiogram to the audiogram at enrollment will determine the stability of the hearing improvement after the end of treatment.

[figure not shown]

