## **9 Safety Assessments**

### **9.1 Adverse Events**

#### **9.1.1 Definition of an Adverse Event (AE) and Adverse Drug Reaction (ADR)**

An adverse event is defined as any untoward medical occurrence in a patient or clinical investigation patient administered a pharmaceutical product and which does not necessarily have to have a causal relationship with this treatment.

An AE can therefore be any unfavorable and unintended sign (including an abnormal laboratory finding, for example), symptom, or disease temporally associated with the use of a medicinal product, whether or not considered related to the medicinal product (ICH E2A).

All AEs should be recorded in the CRFs. If an AE has occurred during the period concerned, this should be noted in the appropriate place.

AEs should be carefully monitored during the entire study.

Examples of AEs include one of the following or a combination of 2 or more of the following factors:

- A new sign, symptom, illness, or syndrome.
- Abnormal laboratory values, if judged clinically significant in the opinion of the investigator. (The parameters fibrinogen, TT, PT, aPTT, are to be excluded)
- Worsening (change in nature, severity or frequency) of a concomitant or pre-existing illness.
- An adverse effect of an invasive procedure required by the protocol.
- An accident or injury.

All AEs fall into the categories “non-serious” and “serious”. The judgment “serious” or “non-serious” should be given by the investigator (refer to 9.1.2)

Surgical procedures or other therapeutic interventions themselves are not AEs, but the condition for which the surgery/intervention is required is an AE and should be documented accordingly. Planned surgical measures and the condition(s) leading to these measures are not AEs, if the condition(s) was (were) known before the period of observation and did not worsen during study. In the latter case the condition should be reported as medical history.

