- b: Performed in premenopausal women who have not been surgically sterilized (documented complete hysterectomy or bi-tubal ligations) or post-menopausal >1 year. Analysis in urine or serum, study drug may not be administered before obtaining pregnancy test results
- c: All medication taken within the last 30 days before Visit 1 should be documented
- d: Physical examination including general appearance (including lymphatic nodes), HEENT (head, eyes, ears, nose and throat), cardiovascular, respiratory, gastrointestinal/abdomen, musculoskeletal, skin/dermatological, neurologic and other examinations  
Otolaryngological examination including otoacoustic emissions, tympanometry, stapedius reflex measurement and ear microscopy
- e: Parameters to be determined in the selected laboratory (local or central) of the site for safety reasons: Fibrinogen, TT, PT, aPTT.  
\*The initial dose of study drug will be adjusted according to the screening fibrinogen concentration assessed in the local laboratory.  
\*\*The assay on day 2 will be performed within 36 hours in the selected laboratory of the site.
- f: The investigator must announce the taking of the blood sample on day 2 for fibrinogen one day before per fax Nordmark and if necessary to the courier company. Nordmark has to be immediately informed in writing (fax) from the responsible laboratory or designee on the result of the coagulation assays on day 2 and 8. The result of the coagulation assay may in principle not be communicated from the laboratory to the investigator or any other blinded study personnel.
- g: Responsible laboratory: Creatinine, aspartate aminotransferase (SGOT; AST), alanine aminotransferase (SGPT; ALT), sodium, potassium, chloride, glucose, urea, uric acid, phosphorus, total bilirubin, total protein, albumin, lactate dehydrogenase (LDH), gamma-glutamyltransferase ( $\gamma$ -GT), alkaline phosphatase, creatinine phosphokinase, triglyceride, cholesterol, high density lipoprotein (HDL), low density lipoprotein (LDL), and very low density lipoprotein (VLDL).
- h: Responsible laboratory: Erythrocytes, hematocrit, MCV, leucocytes, erythrocyte sedimentation rate, hemoglobin, thrombocytes.
- i: Responsible laboratory: Hemoglobin or blood in urine, pH, specific gravity, protein, glucose, ketones, bilirubin, leucocytes.
- j: Air/bone PTA and speech intelligibility test inclusive word recognition

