### 3.2.2. Blinding

The study is carried out in a double-blind, placebo-controlled study design; neither the patient nor the investigator nor any staff collecting, reviewing or cleaning study data have knowledge of the treatment a patient receives. This applies also to any staff analyzing study data at YYY until final unblinding.

To ensure the blinding throughout the study, the following measures are taken:

- Both treatments are indistinguishable in appearance
- Appearance and labeling of vials and treatment kits do not provide any information which disclose the treatment group
- The vials and treatment kits are identified via a kit number only.

In case of medical emergency, or when information about a patient's treatment group is required in order to determine the further treatment of the patient, unblinding of individual patient's treatment can be achieved by opening the respective numbered emergency envelope. Unblinding of patients is also performed for notification of a SUSAR. Investigators have to document immediately every premature unblinding of a patient (e.g. accidental unblinding) in the CRF.

Regular unblinding for all patients including transfer of data on coagulation, biomarkers and anti-ancrod antibodies will only be done for the purpose of the final statistical analysis, after determination of the analysis populations in the BDRM and closure of the database.

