## 10.3. Laboratory Data

Data on laboratory parameters are provided in the CRF or electronically by the central lab. They refer to blood coagulation, clinical chemistry, hematology, biomarkers, antibodies, and urinalysis; relevant for safety purposes are all except biomarkers. If a value is available twice (in the CRF and in the central lab data), both will be listed but only the CRF value will be used for statistical analysis.

All results of laboratory tests will be listed, including reference ranges (available only for central lab data) and possible details on conversion to the standardized units shown in below table. Unusual lab values are reviewed at the BDRM. Values recorded as lower or upper border only will be evaluated as the border (e.g. >140 as 140); however, if all values of a parameter are recorded as border value, the analysis will only be categorical.

The laboratory parameters will be displayed in the analysis in the order as shown in Table 2:

TABLE 2: LABORATORY PARAMETERS

| Group      | Parameter (standardized unit)        |
|------------|--------------------------------------|
| Hematology | Hemoglobin (g/dL)                    |
|            | Hematocrit (%)                       |
|            | Erythrocytes ( $10^6/\mu\text{L}$ )  |
|            | Leukocytes ( $10^3/\mu\text{L}$ )    |
|            | Thrombocytes ( $10^3/\mu\text{L}$ )  |
|            | Mean cell volume ( $\mu\text{m}^3$ ) |

| Group           | Parameter (standardized unit)         |
|-----------------|---------------------------------------|
|                 | ESR (mm/h)                            |
| Blood chemistry | Creatinine (μmol/L)                   |
|                 | GOT/ASAT (U/L)                        |
|                 | GPT/ALAT (U/L)                        |
|                 | Sodium (mmol/L)                       |
|                 | Potassium (mmol/L)                    |
|                 | Chloride (mmol/L)                     |
|                 | Glucose (mmol/L)                      |
|                 | Urea (mmol/L)                         |
|                 | Uric acid (μmol/L)                    |
|                 | Phosphorus (mmol/L)                   |
|                 | Total bilirubin (μmol/L)              |
|                 | Total protein (g/L)                   |
|                 | Albumin (g/L)                         |
|                 | LDH (U/L)                             |

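### Day 8 erythrocyte sedimentation rate is left open while Day 8 coagulation is masked, so allocation may be partly inferable after Day 8 and at the blind data review

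*Combined protocol and SAP*

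**What the plan says.** Protocol 3.1 sets the masking rule for post-dose coagulation on both Day 2 and Day 8: "The result of the coagulation assay may in principle not be communicated from the laboratory to the investigator or any other blinded study personnel". Footnote f of the study schedule (Protocol 17.6) repeats it. The tests covered are fibrinogen, TT, PT and aPTT.

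ESR is classed as hematology. Protocol 8.2.2 has it drawn on Day 1 and Day 8, in a panel listed as "erythrocytes, hematocrit, MCV, leucocytes, erythrocyte sedimentation rate, hemoglobin, thrombocytes". No section limits who sees the result.

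SAP 3.2.2 claims that "neither the patient nor the investigator nor any staff collecting, reviewing or cleaning study data have knowledge of the treatment a patient receives". It defers the transfer of coagulation, biomarker and antibody data until the BDRM has fixed the analysis populations and the database is closed. Hematology is not among the deferred data. ESR is a tabulated parameter in SAP 10.3, which also states: "Unusual lab values are reviewed at the BDRM".

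SAP 9.2.4 and 10.3 provide for values present both in the CRF and in the central laboratory data, and use the CRF value. SAP 9.2.4 applies this to fibrinogen and does not limit it to the screening sample.

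**The concern.** No study drug is given on Day 8, so withholding the Day 8 coagulation result from blinded staff mainly serves the blind. A second Day 8 test that responds to the same drug effect would weaken that protection if left open. The protocol supplies most of the link. Section 2.1 says that "hypofibrinogenemia diminishes the plasma viscosity and tendency of erythrocytes to aggregate", and section 2.4.2 adds: "These rheological changes are sustained and viscosity approaches pretreatment values approximately 10 days after termination of ancrod treatment". The last step, that ESR falls when red cells aggregate less, is general physiology and is not stated in the documents.

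With a pre-dose value from Day 1 and a post-dose value from Day 8, a blinded person could read the change within a patient. This route differs from the Day 2 message that stops further injections, because it is not confined to patients whose fibrinogen falls below 50 mg/dL. At stake are the Day 30 and Day 90 audiograms and physician ratings, adverse-event causality, and the BDRM decisions on per-protocol membership, center pooling and outliers.

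**Working it through.** **Step 1. Compare the safeguards.**

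| Safeguard | Coagulation tests | ESR |
|---|---|---|
| Non-disclosure to the site (Protocol 3.1; 17.6 footnote f) | Covered on Days 2 and 8 | Not covered; footnote h reads only "Responsible laboratory: Erythrocytes, hematocrit, MCV, leucocytes, erythrocyte sedimentation rate, hemoglobin, thrombocytes" |
| Exempt from the investigator's judgement of abnormal values as adverse events (Protocol 9.1.1) | Yes: "The parameters fibrinogen, TT, PT, aPTT, are to be excluded" | No |
| Held back until database closure (SAP 3.2.2) | Yes | No |
| Kept out of BDRM review (SAP 10.3) | Central data not yet transferred; CRF-entered values not addressed | No; reviewed if unusual |

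That the site sees ESR is an inference, but a reasonable one. Investigators must judge abnormal laboratory values with only four tests exempt, and SAP section 2 describes CRF laboratory modules at Screening and Visit 5.

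**Step 2. Is fibrinogen likely to be low at Visit 5?** Visit 4 falls on Day 6 or 7 and Visit 5 on Day 7 to 9, on a different day. Visit 5 is therefore 1 to 3 days after the last scheduled injection. Patients stopped after Day 2 are 5 to 7 days past their last dose. Protocol 2.3 gives medians for 18 healthy subjects after one 0.5 IU/kg infusion, from a baseline of 235 mg/dL:

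- 24 h: 117/235 = 49.8%
- 48 h: 147/235 = 62.6%
- 72 h: 163/235 = 69.4%

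Low fibrinogen at Visit 5 is plausible. The documents give no values for the subcutaneous regimen.

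**Step 3. How well could ESR identify the arm?** The documents give no ESR baseline, SD or change, so the separation between arms is an assumption. Treat the ESR change as normal with equal SD in both arms and means d SDs apart. With 2:1 allocation, always guessing ancrod is right for 2/3 = 66.7%. Measure the fall in SD units from the placebo mean. The best cut-off is c = d/2 − ln(2)/d, and

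accuracy = (2/3)·Φ(d − c) + (1/3)·Φ(c), AUC = Φ(d/√2).

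For d = 1, c = 0.5 − 0.693 = −0.193. Accuracy is (2/3)(0.884) + (1/3)(0.423) = 73.0%.

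| d (SD) | AUC | Correct guesses |
|---|---|---|
| 0.25 | 0.57 | 66.7% |
| 0.5 | 0.64 | 67.5% |
| 1 | 0.76 | 73.0% |
| 1.5 | 0.86 | 79.6% |
| 2 | 0.92 | 85.5% |
| 3 | 0.98 | 93.8% |

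At 0.5 SD or less, ESR adds almost nothing to the 2:1 guess.

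**Step 4. Which decisions come later?** Day 30 and Day 90 audiometry and physician ratings follow the Day 8 draw. At the BDRM the SAP settles analysis sets (4.1), deviation ratings (4.5), outliers and implausible data (5.3), the pooling rule (5.5) and the assessment of model assumptions (5.1).

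**The case against.** The strongest objection is that the central fact, a fall in ESR on ancrod, is outside the documents, so no size can be established. That stands, and it limits the point to a plausible gap. Exclusion criterion 12 removes chronic inflammatory and autoimmune disease. Baseline ESR may therefore be low, leaving little room to fall and making the normal model too optimistic.

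A reader might infer that ESR all but reveals the arm. Take d = −ln(r)/s for a Day 8/Day 1 ratio r and log-scale SD s. A ratio of 0.3 with s of 0.3 to 0.5 gives 90–98% correct guesses. But 0.3 lies below even the 12-hour fibrinogen nadir of 82/235 = 0.35. If ESR moved in proportion to the 48-hour fibrinogen ratio of 0.63, the same model gives 72–80%; at 0.8 it gives 67–70%. The documents do not support near-certain identification.

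A reader might also infer bias in the primary result. The documents do not show it:

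- Primary audiometry and the blood draw belong to the same visit, and no laboratory turnaround is stated.
- The full analysis set keeps every randomized, dosed patient regardless of deviations (SAP 4.1). The per-protocol set is a sensitivity analysis.
- SAP 5.1 performs any transformation or non-parametric alternative for the primary variable in addition to the planned ANCOVA.
- Pooling is to follow external criteria such as country or region (SAP 5.5).

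Nor is an effect on rescue shown, because rescue rests on the Day 8 findings and may be decided before any ESR is reported. Finally, only unusual values are said to be reviewed at the BDRM, and its listings are defined in a separate Data Review Plan that is not available here. This leaves open whether paired ESR values would be seen; it does not show that they are kept out.

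**Conclusion.** The gap is real and modest. Three safeguards name coagulation: non-disclosure, the adverse-event exemption and the data hold-back. None covers Day 8 ESR, and none clearly covers post-dose fibrinogen entered in the CRF. Allocation may be partly inferable in the later secondary assessments, in causality judgements and at the BDRM. The secondary comparisons are exploratory, which limits the consequence. Per-protocol membership matters more than usual because SAP section 2 expects only a few evaluable patients beyond 30. Pooling and outlier handling are the BDRM choices closest to the primary model, and external pooling criteria limit the scope for harm.

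The gain over a 67% guess ranges from essentially nothing to about 19 percentage points (85.5 − 66.7) for separations up to 2 SD. That range rests on an assumed separation, normality, equal variances and an optimal cut-off. The point is worth acting on mainly because the BDRM part costs so little.

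**What to change.** In SAP 3.2.2, 4.5 and 10.3 and in the Data Review Plan, state that post-dose ESR and any CRF-entered post-dose fibrinogen, TT, PT or aPTT are suppressed from all BDRM listings until populations, pooling and model decisions are signed. Release these values with the coagulation data after database closure. This also serves patients already enrolled and costs a few lines of wording.

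For patients still to be enrolled, extend the footnote f non-disclosure wording in Protocol 17.6 to Day 8 ESR, with a matching line in 8.2.2, so that the designated unblinded recipient sees the value instead of the site. This part needs a protocol amendment with ethics committee and authority approval (Protocol 13.2). It helps few patients, since the synopsis plans the last treatment for July 2018. The downside is that blinded investigators lose sight of one Day 8 safety value. The documents attach no eligibility, dosing or stopping rule to it, but its place in adverse-event review (Protocol 9.1.1) would have to be reconciled in the same amendment.
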